**Fig. 2 Fig2:**
[figure not shown]
Illustration of the study design of ANNOTeM over time (Study time scale). For the intervention group there is a comparison group both during the intervention period and during the historical reference period

### Statistical analyses

#### Primary analysis

Because health insurance data will be provided anonymously, we cannot determine the effect of telemedicine consultation on an individual patient level. Rather, we will evaluate the effects of the ANNOTeM concept in clusters. The primary outcome will be analysed as the time from the index visit to the occurrence of the compound outcome as described above. Separate Cox models will be fitted for eligible patients insured at the cooperating health insurance companies, admitted and treated in both, the pre-implementation period and the intervention period. Cox models will comprise sex (m/f only), age and co-morbidity (Y/N) as covariates. Hazard rate ratios will be used to compare time-to-compound event between the two periods. All tests will be performed at a significance level of alpha = 0.05, adjusted for two-sided testing and the k = 6 tests of the primary and secondary analysis. All tests will be performed using the statistics package ‘R’ (version 3.6).

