### Intervention

#### Structure of the network

The teleneurological network ANNOTeM consists of a consortium of four neurocenters (Charité -Universitätsmedizin Berlin, Universitätsmedizin Greifswald, Unfallkrankenhaus Berlin, Epilepsieklinik Tabor) with neurological and epileptological expertise, three health insurance companies (Allgemeine Ortskrankenkasse Nordost, Potsdam (AOK Nordost), Barmer Ersatzkasse, Wuppertal (BARMER), Techniker Krankenkasse, Hamburg (TK)), one technology partner specialized on telemedicine communication products (MEYTEC, Werneuchen, Germany) and the Institute of Public Health, Charité -Universitätsmedizin Berlin,as evaluating institute. The consortium is led by the Charité - Universitätsmedizin Berlin. The clinical centers provide teleneurological care to 11 regional hospitals in the northeastern federal states of Germany (2 in Mecklenburg-Western Pomerania, 8 in Brandenburg and one in Saxony-Anhalt). One regional hospital runs its own neurological department with a certified regional Stroke Unit. In the ten hospitals, the “Neuro Acute Units” were set up as part of the intervention and managed by the respective departments of internal medicine in nine hospitals, whereas in the remaining hospital the “Neuro Acute Unit” is managed as part of an interdisciplinary intensive care unit. In addition, the network cooperates with other neurological, neuroradiological and neurosurgical facilities in the region.

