#### Control group (pre-implementation)

Patients included in the control group were admitted and treated with one of the above mentioned acute neurological diseases in the same cooperating regional hospitals between November 2014 and May 2017, i.e. before start of the ANNOTeM implementation.

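### The stated primary analysis (separate Cox models, no period term, no method for hospital clustering) does not deliver the cluster-based hazard ratio between periods that it promises

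*Protocol article*

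**What the plan says.** The Primary analysis section of the protocol article makes four statements that have to fit together:

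- On the level of evaluation: "Rather, we will evaluate the effects of the ANNOTeM concept in clusters".
- On the model: "Separate Cox models will be fitted for eligible patients insured at the cooperating health insurance companies", continued by "admitted and treated in both, the pre-implementation period and the intervention period".
- On the terms in the model: "Cox models will comprise sex (m/f only), age and co-morbidity (Y/N) as covariates".
- On the effect measure: "Hazard rate ratios will be used to compare time-to-compound event between the two periods".

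On the clusters, the section Structure of the network says "The clinical centers provide teleneurological care to 11 regional hospitals". The section Control group (pre-implementation) says that the control patients were treated "in the same cooperating regional hospitals between November 2014 and May 2017", so each hospital appears in both periods. Study time scale gives one control window for all hospitals, and Table 1 gives a separate recruitment start for each. Sample size calculation mentions no ICC or design effect. Secondary analysis (a log-rank test for a 2 × 2 layout) and Sensitivity analysis add no method for clustering.

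**The concern.** Two things do not fit.

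**The contrast.** A Cox model leaves its baseline hazard unspecified, so the effect of period can be estimated only if period is a term in a model that covers both periods. The plan speaks of separate models and lists no such term. What *separate* refers to is open: it may be the period or the insurer. Neither reading gives one primary hazard ratio with one test.

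**The clusters.** The intervention changes whole hospitals, and the plan announces an evaluation in clusters, but nothing in the stated analysis carries this out. If a pooled model were fitted with the usual model-based standard error, roughly 3640 patients (2 × 1820) would be treated as independent. Any change over time that differs between hospitals would then be missing from the standard error. The hospitals also contribute unequally to the two periods, so without hospital strata a stable difference between hospitals can enter the period contrast.

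At stake are which number is the primary result and the error rate of its test.

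**Working it through.** **1. What the stated models can estimate.**

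- *One model per period.* For period p, h_p(t|x) = h_0p(t)·exp(b_p·x), with x = sex, age, co-morbidity. The partial likelihood removes h_0p(t). The between-period ratio is h_01(t)/h_00(t), and neither fit estimates it.
- *One model per insurer, period implied.* h_j(t|x,z) = h_0j(t)·exp(θ_j·z + b_j·x), with z = 1 in the intervention period and j = 1, 2, 3. This gives three hazard ratios. The article states no rule for choosing or combining them.

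**2. The plan's own figures.** There is no clustering figure to reproduce. The sample size section gives 1820 per group for 39% against 32%, two-sided 5%, 80% power. The ordinary two-proportion formula needs 733 per group. The ratio 1820/733 = 2.48 would match an ICC of (2.48 − 1)/(165.5 − 1) = 0.009, but no design effect is stated, so it does not show that clustering was allowed for. Below, 1820 is used only for the cluster size: m = 1820/11 = 165.5 per hospital and period.

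**3. Unequal windows (Study time scale and Table 1, inclusive days, dates as printed).**

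- Control: 16 Nov 2014 to 31 May 2017 = 928 days for every hospital.
- Intervention: longest 16 Nov 2017 to 31 Jul 2020 = 989 days (989/928 = 1.07); shortest 10 Feb 2019 to 31 Jul 2020 = 538 days (538/928 = 0.58).
- The six hospitals that started before June 2018 supply 6/11 = 55% of control hospital-days. In the intervention period they supply (942 + 989 + 989 + 987 + 862 + 855)/8491 = 5624/8491 = 66%.

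**4. Size of a test with a model-based standard error.** The ICC (ρ) and the between-period cluster correlation (c) are assumptions, because the article gives neither. For the pre-post contrast within hospitals:

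DE = (1 − ρ) + m·ρ·(1 − c); true size = 2·[1 − Φ(z/√DE)], with z = 1.96 at 5% and z = 2.638 at 0.05/6 (if the adjustment for six tests is Bonferroni; the article names no method).

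Example, ρ = 0.01 and c = 0.8: DE = 0.99 + 165.5 × 0.01 × 0.2 = 1.32, so size = 2·[1 − Φ(1.96/1.149)] = 8.8%.

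| ρ | c | DE | size at nominal 5% | size at nominal 0.83% |
|---|---|---|---|---|
| 0.01 | 1 | 0.99 | 4.9% | 0.8% |
| 0.01 | 0.9 | 1.16 | 6.8% | 1.4% |
| 0.01 | 0.8 | 1.32 | 8.8% | 2.2% |
| 0.02 | 0.9 | 1.31 | 8.7% | 2.1% |
| 0.02 | 0.8 | 1.64 | 12.6% | 4.0% |
| 0.05 | 0.9 | 1.78 | 14.2% | 4.8% |
| 0.05 | 0.8 | 2.60 | 22.5% | 10.2% |

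The formula assumes equal hospital contributions, so it leaves out the shift in mix from step 3.

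**5. Simulation with the Table 1 windows.** A Cox model with a period term was fitted under no effect: 11 hospitals, patient numbers proportional to days, 1500 runs per row. The Monte Carlo standard error near 5% is √(0.05 × 0.95/1500) = 0.6 percentage points. SDs are on the log hazard scale.

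| stable hospital SD | hospital-by-period SD | size, no hospital term | size, stratified by hospital |
|---|---|---|---|
| 0.2 | 0 | 6.0% | 5.9% |
| 0.3 | 0 | 6.9% | 5.0% |
| 0.4 | 0 | 7.3% | 4.1% |
| 0.2 | 0.05 | 6.6% | 6.4% |
| 0.2 | 0.10 | 12.7% | 12.0% |
| 0.2 | 0.15 | 19.7% | 20.0% |

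Stratification deals with the shift in hospital mix. It does not deal with hospital-by-period variation, which needs a clustered variance as well.

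**The case against.** The strongest reply has four parts.

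*A period contrast is plainly intended.* The sentence on hazard ratios says so, the hypothesis and the comparison section agree, and adjustment lists often leave out the exposure. This stands. A reader might infer that the plan has no primary estimand, or that no between-period comparison is meant, and the article does not support that. What remains is that the stated models do not produce the intended contrast on one reading, and produce three of them without a combining rule on the other.

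*No hospital term does not mean that the standard error ignores clustering.* A cluster-robust variance needs no model term, the article speaks of clusters, and a condensed article may leave the variance estimator to the analysis plan. This also stands. One cannot infer that patients will be treated as independent, because the article never says so. But it names the model, its terms, the effect measure and a cluster evaluation, and no section connects the last to the others.

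*The inflation is assumed.* With the same hospitals in both periods, stable hospital effects largely cancel: DE is about 0.99 at ρ = 0.01 and c = 1. Quoting a large inflation as fact would go beyond the article, which gives no ICC or between-period correlation. The planned level is also adjusted for six tests, so sizes at nominal 5% are not those of the planned test. The relative inflation at the adjusted level is nevertheless at least as large.

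*The evaluators receive anonymised data*, and a subgroup by hospital type needs only a type flag. So a hospital identifier in the data cannot be taken for granted. Anonymised patient records do not exclude a hospital code, however. The Table 1 dates are specific to each hospital, and an evaluation in clusters requires one.

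**Conclusion.** The point holds as a mismatch within the stated primary analysis, and it should be resolved before the periods are compared. The article promises one between-period hazard ratio evaluated in clusters. Its separate models with three covariates give none (by period) or three without a rule (by insurer), and no hospital stratum, frailty or cluster-robust variance is stated.

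The consequence for the test is conditional. If a model with a period term is fitted with a model-based standard error, the true size at nominal 5% is:

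- about 6–7% if hospital effects are stable (SD 0.2–0.4) and only the mix shifts; the lower end is within simulation error of 5%;
- about 7% to 22% for an assumed ICC of 0.01–0.05 with between-period correlation 0.8–0.9.

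On the same assumptions a Bonferroni level of 0.83% becomes about 1.4% to 10%. The range therefore runs from almost none to large, and the article has no figure that narrows it. It does not support a claim that the error rate is certainly inflated.

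**What to change.** State one primary model: a Cox model on eligible patients from both periods, with an intervention-period indicator as the tested term, sex, age and co-morbidity as covariates, and stratification by hospital. State the variance with it: clustered on hospital with a small-sample correction for 11 clusters or, equally acceptable, a t-test with 10 degrees of freedom on the 11 hospital-level log hazard ratios. Stratification alone is not enough (step 5).

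If the insurers' data cannot be pooled, fit the model per insurer and fix in advance how the results are combined, keeping hospital as the cluster. The same hospitals serve all three insurers, so the insurer estimates are not independent. One way is to combine the insurers within each hospital first and then test across the 11 hospitals.

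Cost: a change of wording and code, and a pseudonymous hospital code in the data passed to the evaluating institute. The confidence interval widens by about √DE, that is by a factor of about 1.08 at DE 1.16 and 1.61 at DE 2.60, and hardly at all if hospital effects are stable. At 1820 per group and 39% against 32%, power with the corrected standard error is about 97%, 93% and 78% at DE 1.32, 1.64 and 2.60 (two-sided 5%). At 0.05/6 it is about 89%, 79% and 54%. These figures use the normal approximation and are slightly optimistic for 11 clusters.

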### Aims

ANNOTeM (acute neurological care in North-East Germany with telemedicine support) aims to improve health care by use of telemedicine for acute time-dependent neurological diseases beyond stroke, in particular coma/status epilepticus, meningoencephalitis, and spinal cord injury, and therefore establish sustainable structures for implementation of evidence based treatments in underserved areas in North-East Germany.

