#### Intervention group (post-implementation)

The intervention group consists of patients treated in one of the eleven cooperating regional hospitals diagnosed with any of the acute neurological diseases (stroke, seizures/status epilepticus, meningoencephalitis, and spinal cord injury) defined in inclusion criteria between November 2017 and July 2020.

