### Comparisons

#### Comparison of control and intervention period in cooperating regional hospitals

Patients with a diagnosis of a defined acute neurological disease and admitted to the cooperating regional hospitals during the intervention period from November 2017 to July 2020 are compared with patients of the same diagnosis group during the control period from November 2014 to May 2017 before the start of the intervention.

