#### Sensitivity analysis

In a sensitivity analysis, we extend the follow-up of the composite primary outcome to 120 days after the index event. Secondly, we perform separate analyses for the outcomes death, first-time nursing home care and paid nursing care for the first time, which together make up the composite endpoint in the primary analysis. Thirdly, we perform a subgroup analysis of the composite primary outcome for following groups: patients with stroke vs other defined acute neurological diseases; patients with vs without nursing care before the index event; patients in cooperating hospitals with vs without neurological departments or telemedicine support before the start of the ANNOTeM intervention. Finally, we investigate patients in the cooperating hospitals with traumatic brain injuries who cannot be included in the main intervention group as a companion study population.

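### The primary Cox analysis lists no diagnosis term, although the design describes a same-diagnosis comparison, so a disease-mix change specific to network hospitals can bias the period hazard ratio

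*Protocol article*

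**What the plan says.** The primary population covers four disease groups, which the section on the intervention group describes as "acute neurological diseases (stroke, seizures/status epilepticus, meningoencephalitis, and spinal cord injury) defined in inclusion criteria". The Inclusion criteria section defines them by ICD-10 main diagnosis.

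Under Comparisons, patients admitted in the intervention period are "compared with patients of the same diagnosis group during the control period from November 2014 to May 2017".

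The Primary analysis section says: "Separate Cox models will be fitted for eligible patients insured at the cooperating health insurance companies", covering both periods. It then gives the covariates, "Cox models will comprise sex (m/f only), age and co-morbidity (Y/N) as covariates", and the effect measure: "Hazard rate ratios will be used to compare time-to-compound event between the two periods". It names no diagnosis covariate or stratum and does not say what the models are separated by.

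The Secondary analysis section compares network with non-network hospitals over the same two periods by a log-rank test for a 2 × 2 layout, again with no covariate or stratum named. The Sensitivity analysis section adds a subgroup analysis of the primary composite in "patients with stroke vs other defined acute neurological diseases".

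**The concern.** The article describes a comparison within diagnosis group, then fixes an adjustment set that does not deliver one. This is not a detail left to a later analysis plan, because the covariate list is explicit.

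It matters because the study compares periods and does not randomise. If the diseases differ in 90-day risk of the composite and their shares change between periods, the period hazard ratio moves even when the intervention does nothing. The bias can go either way.

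The article itself points to ways in which mix could change inside the network only:

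- **Staggered entry.** All hospitals share one control window, but Table 1 gives intervention windows of very different length. The weight of each hospital in the pooled data therefore differs between periods.
- **Admission and coding.** Round-the-clock neurological consultation replaces a neurologist seen the next day at the earliest. Eligibility rests on the main diagnosis and includes a symptom code (R40). Who is admitted, and under which code, may change once a hospital joins.

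**Working it through.** **Inputs from the protocol article.** Sample size calculation: 39% in the control period, 32% in the intervention period, 1,820 patients per group. Primary analysis: alpha 0.05 adjusted for k = 6 tests, taken here as 0.05/6 = 0.0083 because no method is named. Follow-up: 90 days.

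**The plan's own figures.** The article gives no figure for case mix, so there is none to reproduce on this point; 39% and 32% serve as a yardstick. As a constant hazard ratio the planned effect is ln(0.68)/ln(0.61) = 0.78. (The stated 80% power at 1,820 per group does not reproduce: 733 per group suffice at two-sided 5%. That is a separate matter and does not bear on this point.)

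**Assumptions.** Risk 42% in stroke and 27% in non-stroke; non-stroke share 20% in the control period, which returns the overall rate: 0.8 × 42% + 0.2 × 27% = 39%. No true effect.

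**Size of the bias.** Change in overall rate = mix shift × risk difference. Approximate hazard ratio = ln(1 − new rate)/ln(1 − control rate).

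| Mix shift | Risk difference | Overall rate | Approx. HR |
|---|---|---|---|
| 5 points | 15 points | 39% to 38.25% | 0.975 |
| 10 points | 15 points | 39% to 37.5% | 0.95 |
| 20 points | 15 points | 39% to 36% | 0.90 |
| 10 points | 5 points (42% and 37%) | 41% to 40.5% | 0.98 |
| 10 points | 15 points, non-stroke worse (36% and 51%) | 39% to 40.5% | 1.05 |

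To imitate the full 7-point effect at a 15-point risk difference, the mix would have to shift by 7/15 = 47 points.

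**Effect on error rates.** 1,000 simulated trials per row, 1,820 patients per period, exponential times censored at 90 days, first set of risks, no true effect. Each cell gives the mean HR, then the rejection rate at 0.05 and at 0.05/6.

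| Mix shift | Period-only Cox | Stratified by stroke/non-stroke |
|---|---|---|
| none | 1.00; 5.2%; 0.8% | 1.00; 5.2%; 0.9% |
| 10 points | 0.95; 16.2%; 5.3% | 1.00; 6.2%; 1.4% |
| 20 points | 0.90; 47.4%; 22.9% | 1.00; 4.6%; 0.7% |

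With a true hazard ratio of 0.78 and no shift, power at 0.05/6 is 96.4% with or without strata. With a 10-point shift the period-only model returns 0.743 and the stratified model 0.779.

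**How far staggered entry alone could go.** The control window (16 November 2014 to 31 May 2017) is 928 days. From Table 1, the five latest hospitals (KYR, RAT, UEC, GAR, PRE) contribute 624 + 575 + 565 + 538 + 565 = 2,867 intervention days, and the other six 5,624. If all hospitals admit at equal rates (an assumption), the late five fall from 5/11 = 45.5% of patients to 2,867/8,491 = 33.8%, a drop of 11.7 points. If their non-stroke share differed by 20 points from the rest, the pooled mix would move by 0.117 × 20 = 2.3 points, and the hazard ratio to about 0.99 at a 15-point risk difference. A 10-point shift would thus need changed admission or coding as well.

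**The case against.** **Separate models.** The article does not say that one model pools all diseases. A reader might infer it from the covariate list, but the plural wording leaves room for models by diagnosis. This stands: pooling is an inference. It does not remove the problem. If the models are separate by diagnosis, the text does not say which result is primary; if they are not, the same-diagnosis comparison is not made.

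**Same diagnosis group.** The phrase could mean only the same list of eligible diagnoses. That reading is possible, and the text should then say so. The unbalanced mix would remain.

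**Non-network hospitals.** They have identical inclusion criteria and the same two periods, so a regional trend in disease mix or coding should show there too. This stands and narrows the concern to changes specific to network hospitals.

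**Magnitude.** All risks, shares and shifts are assumed, and nothing in the article shows that a shift occurred. The calculation leaves out age and co-morbidity, which may absorb part of the difference between diseases. This stands.

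**Diseases beyond stroke.** The Aims section says the study seeks to "improve health care by use of telemedicine for acute time-dependent neurological diseases beyond stroke", and a reader might infer that this aim goes unanswered. The article does not support that: it plans the stroke versus other diseases analysis on the primary composite, and its hypothesis concerns neurological emergency care as a whole, which a pooled result fits. What remains is limited precision. If non-stroke patients were 20% of 1,820 (364 per period), power for 39% versus 32% would be about 51% at 0.05 and 25% at 0.05/6.

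**Conclusion.** The point holds in a limited form. The stated adjustment set omits diagnosis, the Comparisons section describes a same-diagnosis comparison, and the meaning of the separate models is undefined. A mix change specific to network hospitals would bias the period hazard ratio, and neither the listed covariates nor the non-network comparison reliably removes it.

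Under the assumed risks the bias is moderate: a hazard ratio of about 0.95 for a 10-point shift at a 15-point risk difference, and about 0.98 at a 5-point difference. It can still roughly triple the false-positive rate at 0.05 (16% against 5%). A reader might infer that mix alone could explain a result of the planned size. That would need a 47-point shift at a 15-point risk difference, which is not plausible. The amendment is worth making because it is cheap and removes an avoidable doubt about the primary result.

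**What to change.** 1. Stratify the primary Cox model by the four diagnosis groups of the Inclusion criteria, using the ICD-10 main diagnosis already in the data.
2. Stratify the network/non-network log-rank comparison in the same way.
3. State what the separate Cox models are separated by and, if by diagnosis, which result is primary.
4. Report the number of patients in each diagnosis group by period, for network and non-network hospitals.

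The cost is slightly more analysis work, with no loss of power in the two-stratum simulation. Stratification does not correct for patients recoded from one group to another because of the intervention; the counts in item 4 help to reveal that but do not repair it. The stroke versus other diseases analysis can stay where it is. Its limited precision should be kept in mind when a pooled result is interpreted for diseases other than stroke.

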## Background

The implementation of stroke units [1] along with the advent of intravenous thrombolysis [1] as well as thrombectomy of large vessel occlusion [2] has led to a huge leap in evidence-based acute stroke therapy. However, treatment effects are time-sensitive and depend on swift application of specific therapies. This is not only true for stroke but also for other neurological emergencies like seizures, meningoencephalitis, and spinal cord injury, where fast and effective diagnostication and treatment have been shown to improve outcome [3–5]. Neurological emergencies are a major cause of functional dependence [6]. Hospitals with emergency departments but without a neurology sercive may struggle to provide up-to-date care for patients with neurological emergencies. This applies particularly to rural and other regions with underserved infrastructure. Unfortunately, most neurological diseases peak at higher age, which means that rural areas with typically elderly populations face a particular challenge in providing appropriate care.

Telemedicine networks offer the potential for providing neurological expertise for emergency departments without expert neurologists [7]. In fact, neurological diseases can be adequately assessed via audiovisual examination because typical neurological deficits like palsies, disturbances of speech or consciousness can be reliably captured via video stream [8, 9] and brain imaging is easily transferable digitally.

Telestroke networks have been developed as a blueprint for teleneurological treatment during recent years. Treatment of acute stroke using telemedicine resulted in more frequent and appropriate application of intravenous thrombolysis [10, 11] and was associated with improved outcome [12]. What is more, “telestroke” proved to be cost-effective [13] making stroke one of the most frequent indications for telemedicine in several countries (Refs als from US, Germany etc).

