#### Comparison with non-participating hospitals

In order to investigate whether differences in outcome in the cooperating hospitals may be caused by temporal trends, the composite primary outcome will also be analysed for the same two periods in patients fulfilling the identical inclusion criteria but being treated in hospitals of the same region that do not participate in the network (non-network community hospitals). The non-network hospitals were matched according to geographical location, size and amount of acute neurological cases per year. Data for this comparison are also provided by the three insurance companies.

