#### Secondary analysis

The secondary analysis compares the survival rates obtained in the primary for the network clinics with the group of non-cooperating hospitals using the log-rank-test for 2 × 2 factorial designs (control vs intervention period and network vs non-network hospitals). A treatment effect will be revealed by a significant interaction in favour of the network clinics during the intervention period.

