### Data collection, management, and analysis

#### Data collection methods

The health insurance data for determining the defined outcomes are provided by the cooperating statutory health insurance companies (AOK Nordost, BARMER, TK) in accordance with the defined inclusion criteria. Within the framework of ANNOTeM, pseudonymised personal data of the health insurances will be transmitted in accordance with §75 Social Security Code V to a third trust party, which forwards the data in anonymised form to the evaluating institute. This forwarding has been approved by the supervisory authorities of the participating health insurance companies.

In addition to the account data for identifying the defined outcomes and costs, basic data on age and sex, insurance status and paid nursing care or nursing home care are provided at the beginning of observation.

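### The primary before-after Cox model adjusts for patient mix only through sex, age and one yes/no co-morbidity flag, and omits the baseline nursing-care status that the insurers supply

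*Protocol article*

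**What the plan says.** The primary estimate contrasts two calendar periods: "Hazard rate ratios will be used to compare time-to-compound event between the two periods". Control patients were treated "in the same cooperating regional hospitals between November 2014 and May 2017, i.e. before start of the ANNOTeM implementation", so nothing is randomised. The Primary analysis section of the Protocol article names three covariates: "Cox models will comprise sex (m/f only), age and co-morbidity (Y/N) as covariates". It does not say which conditions count towards a yes.

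Two other mix variables appear only as subgroups, under Sensitivity analysis: "patients with stroke vs other defined acute neurological diseases; patients with vs without nursing care before the index event". Yet under Data collection methods, the insurers' delivery includes age, sex and insurance status, and "paid nursing care or nursing home care are provided at the beginning of observation".

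The article also plans a parallel comparison with matched hospitals outside the network, "In order to investigate whether differences in outcome in the cooperating hospitals may be caused by temporal trends". The Secondary analysis section tests it "using the log-rank-test for 2 × 2 factorial designs (control vs intervention period and network vs non-network hospitals") and names no covariates for that test.

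**The concern.** In a before-after model, the covariates are what separates a change in patients from a change in care. The yes/no coding is a stated choice, not a detail left open for an analysis plan. A two-level flag cannot distinguish one condition from five. If patients in the later period carry fewer conditions, part of their better outcome is credited to the network. If they carry more, a real benefit is partly hidden.

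Baseline nursing care matters for a more direct reason. Two of the three components of the primary outcome are first-time events: first nursing-home care and first paid outpatient care (Primary outcomes). The planned subgroup shows that patients with care before the index event are in the population. Read literally, a patient who already receives one type of care can no longer have that first-time event. A change between the periods in the share of such patients would therefore move the composite hazard whatever the quality of acute care.

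**Working it through.** **Inputs from the Protocol article.** Covariates sex, age and co-morbidity yes/no (Primary analysis); 39% and 32% event rates (Sample size calculation); 90-day follow-up (Primary outcomes). The article gives no figure for residual confounding, so there is none to reproduce.

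**Yardstick.** Under proportional hazards the planned effect is HR = ln(1 − 0.32)/ln(1 − 0.39) = ln 0.68/ln 0.61 = 0.78.

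**Assumptions, none from the article.** The form of the co-morbidity score, its mean, the size of the shift, and the hazard ratio per condition or per standard deviation. Age and sex are left out of the illustration.

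**Step 1: share of a small shift left after yes/no adjustment, normal score.** With p the share coded yes and c the cut-point, the share left is 1 − φ(c)²/[p(1 − p)]. At p = 50%: φ(0) = 0.399, so 1 − 0.159/0.25 = 0.36. Likewise 0.42 at 30% or 70%, 0.51 at 20% or 80%, 0.66 at 10% or 90%, and 0.78 at 5% or 95%.

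**Step 2: the same share for a count coded any versus none** (least-squares slope of the count on period, given the flag):

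| Mean count | Poisson | Negative binomial (k = 1.5) |
|---|---|---|
| 0.3 | 16% | 22% |
| 0.5 | 25% | 33% |
| 1 | 45% | 50% |
| 2 | 73% | 69% |
| 3 | 87% | 78% |

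Over steps 1 and 2 the range is 16% to 87%.

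**Step 3: effect on the hazard ratio when the true period effect is nil.** Poisson counts capped at 8, exponential hazards set to a 39% control risk at 90 days, HR 1.25 per condition. Expected events and exposure are fitted with a Poisson rate model:

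| Mean count, control to intervention | Coded yes | Unadjusted | Yes/no | Graded count |
|---|---|---|---|---|
| 2.5 to 2.2 | 92% to 89% | 0.934 | 0.947 | 1.00 |
| 2.0 to 1.6 | 86% to 80% | 0.912 | 0.938 | 1.00 |
| 2.0 to 1.8 | 86% to 83% | 0.955 | 0.968 | 1.00 |
| 1.0 to 0.8 | 63% to 55% | 0.954 | 0.980 | 1.00 |
| 0.5 to 0.4 | 39% to 33% | 0.977 | 0.994 | 1.00 |

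Share left in the second row: ln 0.938/ln 0.912 ≈ 0.69. In the fourth: ln 0.980/ln 0.954 ≈ 0.43. Against the planned effect on the log scale, ln 0.938/ln 0.780 ≈ 0.26 and ln 0.980/ln 0.780 ≈ 0.08.

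**Step 4: check with a fitted Cox model.** Simulation with 200,000 patients per period, no true effect, censoring at 90 days. A normal score falling by 0.3 SD (log HR 0.3 per SD) gives 0.909 unadjusted. With the flag it gives 0.963 when 44% are coded yes (36% left) and 0.937 when 87% are (65% left). With the full score in the model the estimate lay between 0.99 and 1.01 in every scenario run.

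**The case against.** **The share left is unknown.** A reader might infer that the flag leaves most of a co-morbidity shift in place, because an elderly population would nearly all be coded yes. The article does not support that. It says "most neurological diseases peak at higher age", which concerns age and not co-morbidity, and it gives neither a definition of yes nor its prevalence. More than half remains only in part of the assumed range: about 80% or more (or 20% or less) coded yes on a normal score, or a count with a mean above roughly 1. Elsewhere the flag removes most of the shift.

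**There is a parallel control.** It would be wrong to say that covariates are the plan's only protection. The non-network comparison can absorb a shift common to both hospital groups, and the article's Discussion names time trends as a limitation. What remains is that this comparison cannot absorb a shift confined to the network hospitals and leaves the primary hazard ratio as it is. One route to such a shift exists: in Table 1, four of the eleven hospitals start recruitment only in January or February 2019, so hospitals weigh differently in the two periods, and the listed covariates include no hospital term. That shows a route, not a size.

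**The illustration is one-sided.** Any part of a shift that travels with age is already adjusted. The assumed falls have no source, and a rise would bias against the intervention. Both points stand. Co-morbidity is also not acute severity, so nothing here measures the effect of a change in severity.

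**A graded count can itself mislead.** Suppose true co-morbidity is unchanged (mean 2.0, HR 1.25 per condition) but coding adds 0.4 diagnoses per patient in the later period. The same model then gives 1.00 unadjusted, 0.979 with yes/no and 0.914 with the graded count. With 0.2 added it gives 1.00, 0.988 and 0.954. This is a serious argument against counting diagnoses coded during the index stay, which the new units and documentation could affect. Restricting to earlier diagnoses answers that part. A general drift in coding would remain possible, which is why the yes/no model should be kept alongside.

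**Conclusion.** The point holds as a limited and inexpensive improvement. The primary model as fixed removes only part of a change in patient mix. For co-morbidity, between about 16% and 87% of a shift stays in the hazard ratio, depending on facts that the article does not give. In the worked cases the spurious hazard ratio runs from 0.994 to 0.938, that is, from about 2% to 26% of the planned effect on the log scale. These figures rest on assumed shifts and an assumed hazard ratio of 1.25 per condition. They show what could happen and do not show that a shift occurred or in which direction. The omission of baseline nursing-care status needs no such assumption: the variable is supplied, it bears directly on the first-time components, and it is not in the model.

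**What to change.** 1. Add nursing-care status before the index event as a covariate in the primary Cox model. The insurers already deliver it, so the cost is one term.
2. Replace the yes/no flag with a graded co-morbidity score, built only from diagnoses recorded before the index admission, with the same look-back window in both periods and both hospital groups.
3. Keep the yes/no model as a sensitivity analysis. A marked difference between the two results would call for a check on coding intensity by period.

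With at least 1820 patients per group and 39% assumed control risk (1820 × 0.39 ≈ 710 control events), the extra parameters are affordable. The costs are a look-back window that must be fixed in advance and confirmation that diagnosis-level data reach the evaluating institute. The article lists account data and basic characteristics but does not say so. If those data are not available, the first change can still be made alone. A change in coding intensity between periods remains a risk for any graded score.
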